#### Secondary outcomes

In addition to scores on GAD-7, we will examine whether or not each participant demonstrated remission and reliable remission on the GAD-7 from baseline to 6 weeks post-intervention and baseline to 10 weeks follow-up. We will report and compare between groups the percentage of participants demonstrating remission (scores of <10 on the GAD-7; [35]) and reliable remission where participants experience remission and a change score reduction of ≥5 [35], which is greater than the known unreliability of the measure [40], at both time points.

#### Worry

Worry will be measured using the 16-item Penn State Worry Questionnaire (PSWQ; [41]). The PSWQ will be administered at all time points. Each item is rated using a five-point Likert scale ranging from 1 (“not at all typical of me”) to 5 (“very typical of me”). Total scores range from 16 to 80, with higher scores indicating greater degree of worry. The PSWQ has been shown to have good validity and reliability, including internal consistency, factorial validity and convergent and discriminant validity [42].

#### Depressive symptoms

Depressive symptoms will be assessed using the nine-item Patient Health Questionnaire (PHQ-9; [43]), administered at all time points. Items ask participants to indicate how often they have been bothered by symptoms over the last 2 weeks. Responses are given on a four-point Likert scale ranging from 0 (“not at all”) to 3 (“nearly every day”). Total scores range from 0 to 27, with higher scores indicating greater severity of symptoms. The PHQ-9 has been shown to have good validity and reliability, including internal consistency, test–retest reliability, sensitivity to change and criterion validity [44]. Participants experience remission if they score <10 and reliable remission if they both remit and reduce by ≥6 [45].

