### Participants

For inclusion in this trial, participants must: 1) be aged 18 years or older; 2) score 10 or higher on the GAD-7 [35] indicating at least moderate GAD symptom severity; 3) screen positive for a GAD diagnosis on a digital version of the Mini-International Neuropsychiatric Interview (MINI) version 7 for DSM-5 [36], followed by telephone verification (see Procedure below for details); 4) be either not on prescription medication for anxiety, depressive symptoms, or poor sleep, or on a stable dose for at least 4 weeks; and 5) must not be currently receiving or have previously received CBT for anxiety in the last 12 months (this inclusion criterion was included after a modification was made by the ethical review committee after recruitment start). We will exclude participants who self-report: 1) being diagnosed with any of the following conditions: schizophrenia, psychosis, bipolar disorder, seizure disorder, substance use disorder; 2) having recent trauma to the head or brain damage; 3) having severe cognitive impairment; 4) having serious physical health concerns necessitating surgery or with a prognosis of less than 6 months; or 5) being pregnant. Individuals with other anxiety or related disorders (e.g. panic disorder, social anxiety disorder, and so forth) were included in the study as long as they endorsed worry (consistent with a GAD diagnosis) as their primary concern assessed at telephone screening.

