#### Sleep difficulty

Sleep difficulty will be measured using the eight-item Sleep Condition Indicator (SCI-8; [46]), administered at all time points. Total scores range from 0 to 32, with higher scores indicating better sleep. The SCI-8 has been shown to have good validity and reliability, including internal consistency, convergent validity and sensitivity to change [46]. Participants experience remission if they score >16 and reliable remission if they both remit and reduce by ≥7 [46].

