### Statistical analysis

Analyses will be carried out using Stata [52]. In accordance with the CONSORT statement [38], we will report all participant flow in each arm (see Fig. 1). Descriptive statistics of participant recruitment, study dropout and intervention engagement will be reported. Baseline characteristics will be presented by randomised group and summarised by means and standard deviations for continuous measures, or number and percentage for categorical measures.

To test the primary hypothesis, treatment effects on GAD symptom severity (GAD-7) will be estimated using linear mixed models fitted to data at all core time points (baseline, 3 weeks mid-intervention, 6 weeks post-intervention, 10 weeks follow-up). Fixed effects will be baseline assessment for GAD-7, randomised group, time (categorical), and time by group interactions. Participant ID will be included as random intercepts to allow for repeated measures. Marginal treatment effects will be estimated for GAD-7 at each time point and reported separately as mean-adjusted differences in scores between the randomised treatment groups with 95% confidence intervals and two-sided *P* values. The analysis will use statistical techniques for handling missing data under a missing-at-random assumption. Secondary hypotheses will be tested using analogous analyses. For the binary secondary outcome (whether participants achieved remission and reliable remission on GAD-7, PHQ-9 and SCI-8 outcomes), the same approach will be followed using logistic mixed models. All primary and secondary analyses will be conducted on an intention-to-treat basis, including all participants who were randomised, with no planned interim analysis.

Additional sensitivity analyses will be conducted to test primary and secondary hypotheses using data from participants who receive and engage with the intervention, defined as those who: 1) download the app; 2) complete at least two modules of digital CBT; and 3) complete all modules. Separate sets of analyses will be conducted for each of these three categories of intervention completion.

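### PHQ-9 and SCI-8 remission is scored in all randomised participants without requiring baseline caseness, so the reported percentages would not be remission rates

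*Protocol article*

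**What the plan says.** **Definitions.** The Depressive symptoms section of the Protocol article states: "Participants experience remission if they score <10 and reliable remission if they both remit and reduce by ≥6". The Sleep difficulty section uses the same form: "Participants experience remission if they score >16 and reliable remission if they both remit and reduce by ≥7". Neither sets a condition on the baseline score.

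**Eligibility.** Under Participants, the one symptom-score threshold is to "score 10 or higher on the GAD-7", alongside a positive screen for a GAD diagnosis. Depression and sleep enter the inclusion criteria only through medication, since participants must "be either not on prescription medication for anxiety, depressive symptoms, or poor sleep, or on a stable dose for at least 4 weeks".

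**Analysis.** Under Statistical analysis, the binary secondary outcomes are "whether participants achieved remission and reliable remission on GAD-7, PHQ-9 and SCI-8 outcomes". They are analysed by logistic mixed models following the approach of the primary model, which has the baseline score as a fixed effect. The population is fixed in the same section: "All primary and secondary analyses will be conducted on an intention-to-treat basis, including all participants who were randomised".

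**The concern.** Remission means that a condition was present and has gone. For the GAD-7 the definition works, because eligibility makes every participant a case (10 or more) at entry. The same form has been carried over to two scales on which participants need not be cases at entry.

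Two things are at stake for these secondary outcomes. First, the published percentages would carry a label they do not deserve, and readers could compare them with true remission rates from other trials. Second, the treatment contrast would answer a blended question: how often cases cross the cut-off, combined with how often people who were never cases stay on the well side of it.

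**Working it through.** **What follows from the definitions alone**

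| Baseline PHQ-9 | Remission (below 10) | Reliable remission (below 10 and a fall of at least 6) |
|---|---|---|
| 0–5 | Counted at any visit with a score below 10, even with no change | Impossible: the largest fall is the baseline score itself, at most 5 |
| 6–9 | Counted at any visit with a score below 10, even with no change | Possible (for example 9 to 3), though never a case |
| 10 or more | Counted only after crossing the cut-off | Possible, with its intended meaning |

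A participant unchanged at PHQ-9 5 is a success on one endpoint and an unavoidable failure on the other. On the SCI-8, a participant unchanged at 25 is counted as remitted.

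**Size of the effect on remission**

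The plan gives no figure for PHQ-9 or SCI-8 remission. Its only calculation is for the GAD-7, and it reproduces: 2 × (1.960 + 1.282)² / 0.50² = 84.1, so 85 per arm and 170 in total; 170 / 0.70 = 243, against 242 stated. The sample size is not at issue.

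Let q be the share of participants who are non-cases at baseline, p the proportion of cases in remission at follow-up, and s the proportion of non-cases on the well side at follow-up. In each arm:

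reported proportion = (1 − q) × p + q × s

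The between-arm difference is then:

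reported difference = (1 − q) × (difference in cases) + q × (difference in non-cases)

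Plain remission is inflated in an arm whenever s exceeds p. The difference is smaller than that in cases whenever non-cases benefit less than cases.

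The documents give none of q, p or s. Assume p = 30% on waitlist and 50% on digital CBT, with s = 100% in both arms (no effect in non-cases):

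| q | Waitlist | Digital CBT | Difference |
|---|---|---|---|
| 0% | 30% | 50% | 20 points |
| 20% | 0.8 × 30 + 20 = 44% | 0.8 × 50 + 20 = 60% | 16 points |
| 30% | 0.7 × 30 + 30 = 51% | 0.7 × 50 + 30 = 65% | 14 points |
| 40% | 0.6 × 30 + 40 = 58% | 0.6 × 50 + 40 = 70% | 12 points |
| 50% | 0.5 × 30 + 50 = 65% | 0.5 × 50 + 50 = 75% | 10 points |

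With s = 90% in both arms the percentages fall slightly, but the differences are unchanged because s cancels.

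**If non-cases also benefit**

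Suppose instead that treatment lowers everyone's PHQ-9 by 2.5 points. The other assumptions are a baseline mean of 11 and SD of 5 (38% non-cases), a 1-point waitlist improvement, 85 per arm, and baseline–follow-up correlations of 0.5 to 0.8. Simulation gives a difference of 21 to 24 points in cases and 13 to 17 points in non-cases. In all randomised participants this is about 20 points: 0.62 × 21 + 0.38 × 17 = 19.5, and 0.62 × 24 + 0.38 × 13 = 19.8. The dilution is then slight, but the percentages are still not remission rates.

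**The case against.** **Power.** A reader might infer that counting non-cases costs power. An unadjusted two-proportion test with no effect in non-cases suggests this: at q = 40%, power is about 37% with 85 per arm, against 54% in the 51 cases per arm. The documents do not support the inference, for two reasons.

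- The planned model adjusts for baseline. Under the same no-effect assumption, adjusting for baseline case status narrows the gap to roughly 45% against 54%.
- Nothing in the protocol says that non-cases cannot benefit. Waitlist participants entering at PHQ-9 6 to 9 can worsen past the cut-off, and treatment may prevent that. In the uniform 2.5-point scenario, with a baseline covariate but no random intercept, power is about 79% to 89% in all randomised participants and 62% to 75% in cases only, for correlations of 0.5 to 0.7. With an effect proportional to the baseline score, the two are roughly equal.

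This part of the objection stands in full.

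**Remitted at every visit.** A reader might also infer that non-cases count as remitted throughout. They do so only while the score stays on the well side of the cut-off.

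**Left to the analysis plan.** The protocol refers to a detailed analysis plan that is not shown, and denominators are often settled there. Here, however, the protocol itself fixes both the definition and the population, and a restriction to baseline cases would contradict its all-randomised statement as written. The point is a stated rule rather than an omission.

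**Low consequence.** The hypotheses in the Background concern depressive symptoms and sleep difficulty, which the continuous scores address in everyone. That is fair. It limits the weight of the point but does not correct the label.

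**Intention to treat.** Restriction might seem to breach it. It does not, because Table 1 places both scales at baseline, before allocation, and participants would still be analysed as randomised.

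**Conclusion.** The point holds as a matter of definition and estimand. As written, PHQ-9 and SCI-8 remission includes people who never had the condition, and PHQ-9 reliable remission contains certain failures (baseline 0 to 5) as well as possible successes among non-cases (6 to 9). This follows from the text without any assumed figure.

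The numerical effect cannot be fixed from the documents. It runs from a difference cut in proportion to the non-case share, if non-cases do not benefit, to very little change, if they benefit nearly as much as cases. No loss of power is claimed.

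Only secondary binary outcomes are affected. The primary GAD-7 analysis, GAD-7 remission and the sample size are untouched. The change is worth making because it is cheap and prevents mislabelled results.

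**What to change.** - Define PHQ-9 remission and reliable remission among participants with baseline PHQ-9 of 10 or more, and SCI-8 remission among those with baseline SCI-8 of 16 or less. Analyse them as randomised and report the number at risk in each arm.
- Keep all randomised participants in the continuous PHQ-9 and SCI-8 analyses.
- If the all-randomised proportions are still wanted, report them under a neutral label: below the clinical cut-off (PHQ-9) or above the cut-off (SCI-8).
- Settle the direction of the SCI-8 reliable-remission rule at the same time. It is a separate error, but it interacts with this fix. The scale is described thus: "Total scores range from 0 to 32, with higher scores indicating better sleep". A required reduction of at least 7 ending above 16 needs a baseline of at least 17 + 7 = 24, so as worded no baseline case could meet it.

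**Cost.** One or two sentences in the protocol and analysis plan. The denominators shrink, power for these binary outcomes may fall, and the subgroups are open to chance imbalance because the protocol describes blocked randomisation with no stratification on either scale.

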#### Sleep difficulty

Sleep difficulty will be measured using the eight-item Sleep Condition Indicator (SCI-8; [46]), administered at all time points. Total scores range from 0 to 32, with higher scores indicating better sleep. The SCI-8 has been shown to have good validity and reliability, including internal consistency, convergent validity and sensitivity to change [46]. Participants experience remission if they score >16 and reliable remission if they both remit and reduce by ≥7 [46].

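### SCI-8 reliable remission requires the score to fall by at least 7 on a scale where higher is better, so the rule selects deterioration and excludes recovery

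*Protocol article*

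**What the plan says.** In the protocol article, the Sleep difficulty subsection of Measures fixes the direction of the SCI-8: "Total scores range from 0 to 32, with higher scores indicating better sleep". It then gives two binary definitions: "Participants experience remission if they score >16 and reliable remission if they both remit and reduce by ≥7".

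The Statistical analysis section lists the binary secondary outcomes as "whether participants achieved remission and reliable remission on GAD-7, PHQ-9 and SCI-8 outcomes" and assigns them to logistic mixed models, analysed by intention to treat. Sleep difficulty is one of the secondary outcomes named in the Background, at both 6 and 10 weeks.

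The two neighbouring scales have parallel rules. For the PHQ-9, "Total scores range from 0 to 27, with higher scores indicating greater severity of symptoms", and the rule is "Participants experience remission if they score <10 and reliable remission if they both remit and reduce by ≥6". For the GAD-7, remission is a score below 10, and the article defines "reliable remission where participants experience remission and a change score reduction of ≥5". Nothing in the article says that SCI-8 change is reverse-scored.

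**The concern.** On the GAD-7 and PHQ-9 a lower score is better, so a required reduction is a required improvement. The SCI-8 runs the other way. Its remission threshold has been turned round accordingly (above 16 rather than below a cut-off), but the change requirement still asks for a reduction. The sentence looks like the PHQ-9 sentence with only one of its two directions adapted, although the article does not say how it arose.

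A responder definition that is followed literally has to count responders. This one counts people whose sleep worsened by at least 7 points from a high starting level, and leaves out everyone who moved from poor to good sleep. If the derived variable is programmed from this text, an intervention that improves sleep lowers the rate of the outcome that is meant to show its benefit.

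**Working it through.** **Inputs, all from the article.** SCI-8 range 0 to 32, higher is better; remission is a score above 16; reliable remission is remission plus a reduction of at least 7 (Sleep difficulty). PHQ-9 range 0 to 27, cut-off below 10, reduction at least 6 (Depressive symptoms). GAD-7 range 0 to 21, cut-off below 10, reduction at least 5 (Primary outcome and Secondary outcomes); entry requires a score of 10 or more (Participants). There is no stated figure to reproduce, because the question is the direction of a rule.

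**Step 1: who can meet the rule as written.** Let b be the baseline score and f the follow-up score, both whole numbers. The rule is f ≥ 17 and b − f ≥ 7.
- Smallest possible baseline: b ≥ 17 + 7 = 24.
- Largest possible follow-up score: f ≤ 32 − 7 = 25.
- For each f from 17 to 25, b runs from f + 7 to 32, which is 26 − f values. The total is 9 + 8 + … + 1 = **45 pairs**.

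In every pair f is below b, and b is already above the remission cut-off. None has a baseline of 16 or less.

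**Step 2: the rule with the change reversed.** Now f ≥ 17 and f − b ≥ 7.
- For each f from 17 to 32, b runs from 0 to f − 7, which is f − 6 values. The total is 11 + 12 + … + 26 = 16 × 37 / 2 = **296 pairs**.
- All are improvements, with baselines from 0 to 25. Of these, 251 start at 16 or below and 45 start above 16.
- The overlap with the 45 pairs in Step 1 is **zero**.

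| Baseline → follow-up | Sleep | As written | Reversed |
|---|---|---|---|
| 8 → 20 | better | no | yes |
| 8 → 28 | better | no | yes |
| 16 → 23 | better | no | yes |
| 28 → 18 | worse | yes | no |
| 24 → 17 | worse | yes | no |

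**Step 3: same check on the sister scales.** For the PHQ-9, f ≤ 9 and b − f ≥ 6 gives 175 pairs, all improvements. For the GAD-7, with baseline 10 to 21, f ≤ 9 and b − f ≥ 5 gives 110 pairs, all improvements. The fault is confined to the SCI-8.

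**Step 4: an illustration of rates.** The article gives no SCI-8 distribution, so these inputs are assumptions: normal scores with baseline mean 14, SD 6, baseline to follow-up correlation 0.6, a gain of 1 point in controls and 4 points in the treated arm.

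| Rule | Control | Treated |
|---|---|---|
| As written | 1.0% | 0.5% |
| Reversed | 10.4% | 25.4% |

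With 121 per arm, before attrition, the rule as written gives 121 × 0.010 ≈ 1.2 events against 121 × 0.005 ≈ 0.6. The reversed rule gives about 12.6 against 30.7.

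Varying the mean over 12 to 16, the SD over 5 to 7 and the correlation over 0.4 to 0.7 (27 scenarios, same gains):
- As written: 0.1 to 3.0% in controls and 0.02 to 2.3% in the treated arm, with the treated arm lower in all 27.
- Reversed: 4 to 19% in controls and 17 to 32% in the treated arm, with the treated arm higher in all 27.

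**The case against.** The strongest reply is that the intended meaning is clear from the subsection itself. It states the scale direction, the cut-off points upward, the word remit implies improvement, and under a heading about sleep difficulty a reduction might loosely mean less difficulty. That makes the intention recoverable, but it does not make the sentence right: both criteria are stated in SCI-8 points, and those rise as sleep improves.

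A second reply is that a misleading reversed result is unlikely to reach print. With about one event per arm, a logistic mixed model could hardly be fitted, and the near-empty variable would expose the mistake. This is fair. The more likely harm is an unusable endpoint and an unplanned repair after the data are seen, rather than a published finding of harm.

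A third is that the reach is narrow, and that also stands. The error affects one component of one derived binary variable for one secondary measure. The article's sleep hypotheses are worded as improvement in sleep difficulty, which the continuous SCI-8 analysis tests.

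The analysis plan, which is not shown, may define the variable correctly. Even so, the article states a rule and states it in the wrong direction; if the plan differs, the two need to be reconciled in writing.

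**Conclusion.** The concern holds. By arithmetic alone, and with no outside assumption, SCI-8 reliable remission as written can be met only by participants who start at 24 or more and fall by at least 7 points. It shares no case with the rule that the scale direction implies. A pre-specified secondary outcome therefore measures the opposite of its name and must be corrected before it is derived.

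The percentages in the illustration rest on assumed distributions and show direction and sparseness only; the conclusion does not depend on them. The primary GAD-7 outcome, the sample size, the continuous SCI-8 analysis, simple SCI-8 remission, and the GAD-7 and PHQ-9 rules are all unaffected. Whether 7 points is the right size of change rests on a cited source that is not available here, and is not questioned.

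**What to change.** Reword the definition so that SCI-8 reliable remission means a score above 16 together with an increase of at least 7 points from baseline. Make the same change wherever the analysis plan repeats the rule, and record it as a correction of direction made before unblinding or, failing that, with its date.

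Check the derivation code against two test cases: 8 → 20 must count and 28 → 18 must not.

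One optional clarification can go in at the same time. The SCI-8 is not an entry criterion, so some participants may start above 16, and the corrected rule can still count them if they rise by 7 or more (baselines 17 to 25). The plan could say whether that is intended.

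The cost is one word in the text and one line of code, with no effect on data collection or sample size.

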#### Wellbeing

Positive mental wellbeing will be assessed using the 14-item Warwick–Edinburgh Mental Wellbeing Scale (WEMWBS; [47]). Items ask participants to indicate how often they have particular experiences over the last 2 weeks. Responses to items are given on a five-point Likert scale ranging from 1 (“none of the time”) to 5 (“all of the time”). Total scores range from 14 to 70, with higher total scores indicating greater wellbeing. The WEMWBS has good validity and reliability, including factorial validity, internal consistency, test–retest reliability, and convergent and discriminant validity [47].

#### Quality of life

Quality of life will be assessed using the individualised Patient-Generated Index measure [48]. The Patient-Generated Index will consist of two parts in which participants are asked to: 1) identify the three most important areas of their lives affected by their anxiety; and 2) for each area identified, indicate the degree to which this area has been affected by their anxiety in the past month, from 0 (“the worst you could imagine”) to 100 (“exactly as you would like to be”). The Patient-Generated Index has been shown to have good validity and reliability [49].

